#### 2.3.2. Outcome Measures

We will report on clinical and qualitative outcomes relating to CURATE.AI’s effect, implementation, and acceptability. The following clinical outcomes will be reported:Proportion achieving blood pressure and glycaemic control at four months.Average number of days until blood pressure or glycaemic control is first achieved.Proportion relapsing after disease control is achieved (i.e., high blood pressure).Proportion compliant with clinic follow-up.Proportion compliant with home monitoring of blood pressure or glucose.Number of dropouts.Proportion of dosing decisions recommended by CURATE.AI but not implemented at the physician’s discretion and the magnitude of difference.

The study’s main purpose is to explore the feasibility of the CURATE.AI system in clinical practice and not to establish efficacy or effectiveness. The clinical outcomes are included to show the preliminary effects of the intervention. Qualitative work will seek to understand the practicalities of using the system in clinical practice, identify implementation barriers and enablers that can inform future development of the system, and to advance the processes associated with using CURATE.AI.

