Participants will be followed up monthly for four months. Clinically, blood pressure may be controlled with medication within four to six weeks [33]. For type II diabetes, although traditionally changes in HbA1c are assessed every three months, emergent evidence suggests clinically relevant changes may occur as early as one month [34]. Based on these data, four months was deemed appropriate to observe clinical improvements as well as being a sufficient period to test the system. Clinic visits may be face-to-face or virtual as appropriate. If a dosage change is required at a clinic visit, hypertensive participants will be asked to monitor their ambulatory blood pressure for a single six-hour period at home (once hourly). A six-hour ambulatory blood pressure recording is equivalent to a twenty-four-hour reading [35]. Patients will then continue to monitor blood pressure twice daily, morning and evening, for up to seven days. Following any change of type II diabetic medications, patients will be asked to wear a continuous glucose monitoring device for a minimum of seven days at home (the maximum wear time is fourteen days). Monitoring will commence fifteen days after the dose change is initiated (for either hypertensives or type II diabetics), so a steady state can be reached before assessment. These data will feed back into the CURATE.AI system, and further recommendations on dose adjustment will be generated if required. The treating physician will regularly review remote monitoring data for safety. If the patient’s medication is changed entirely, recalibration with CURATE.AI is required. At the last clinic visit, patients will be interviewed using a semi-structured survey on their experiences with the CURATE.AI system. 

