#### 2.3.5. Data Analysis

All analyses will be conducted using STATA version 15.0 (STATA Corp, College Station, TX, USA). As appropriate, summary statistics will be presented as means with standard deviation, medians with interquartile ranges, and percentages. Clinical outcomes will be analysed separately for the hypertensive and type II diabetic groups. Blood pressure control is defined as a home or ambulatory blood pressure of less than 135/85 mmHg or office readings below 140/90 mmHg, unless otherwise defined by the treating physician [39]. Glycaemic control is defined as HbA1c < 7% [40] or glycaemic variability ≤ 36% or time in normal range (4.0 to 10.0 mmol/L) > 70% [41]. The proportion of patients achieving blood pressure control and glycemic control will be calculated by comparing the baseline reading to the four-month follow-up. A within-subject analysis of hypertensive and glycemic control will be conducted using the Chi^2^ or McNemar’s test, if cell counts are small (<5). The proportion achieving clinically relevant reductions in systolic and diastolic blood pressures by the four-month follow-up will be determined. The number of days until blood pressure or glycaemic control is first achieved will be calculated. The occurrence of relapse after control has been achieved (i.e., high blood pressure) will also be determined. 

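### The average number of days to first control has no value for patients who never reach control, so as worded it is a responders-only figure that barely reflects how many respond

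*Protocol article*

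**What the plan says.** Section 2.3.2 of the protocol article (Outcome Measures) lists "Average number of days until blood pressure or glycaemic control is first achieved" among the clinical outcomes. Section 2.3.5 (Data Analysis) adds "The number of days until blood pressure or glycaemic control is first achieved will be calculated" and, for all outcomes, that "summary statistics will be presented as means with standard deviation, medians with interquartile ranges, and percentages", as appropriate. No time-to-event method is named.

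Three other parts of the article bear on this:

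- **Entry and follow-up.** The exclusion criteria remove anyone whose HbA1c or blood pressure is already controlled at baseline. Section 2.3.3 states "Participants will be followed up monthly for four months".
- **Definition of control.** "Blood pressure control is defined as a home or ambulatory blood pressure of less than 135/85 mmHg or office readings below 140/90 mmHg", unless the treating physician sets another target. "Glycaemic control is defined as HbA1c < 7% [40] or glycaemic variability ≤ 36% or time in normal range" above 70%. Neither definition mentions confirmation at a later assessment.
- **Companion outcomes.** Section 2.3.2 also lists the proportion controlled at four months, the number of dropouts, and "Proportion relapsing after disease control is achieved (i.e., high blood pressure". Section 2.3.5 analyses the two disease groups separately.

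Section 2.3.2 describes the clinical outcomes as preliminary and says the study is not meant to establish efficacy.

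**The concern.** Days to first control is a time-to-event outcome observed over a fixed window. Because nobody is controlled at entry, each patient either has a date of first control or leaves observation without one. The second kind of patient has no number to put into an average. Computed as worded, the average drops these patients without saying so.

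Two things follow. The figure is biased towards fast control, because the slowest patients are the ones left out and the window caps it at about 120 days. It is also insensitive to the main feature of the result, which is how many patients reach control. A treatment that controls a few patients and one that controls most can show similar averages.

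This matters even in a feasibility study. The Discussion says the data will inform a later efficacy evaluation and expresses the hope that dosing can be optimised more rapidly. Days to control is the outcome that speaks to that hope.

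**Working it through.** The article gives no expected number of days and no response rate, so there is no figure of its own to reproduce. What follows is an illustration.

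**Inputs from the article.** Four monthly visits, taken as days 30, 60, 90 and 120; 20 patients per disease group; all uncontrolled at baseline.

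**Assumption.** A constant chance h of first control at each visit among those not yet controlled, with no dropout. The article gives no value, so h runs from 0.1 to 0.4.

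**Formulas.**

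- Chance of first control at visit k: p(k) = h(1−h)^(k−1), for k = 1 to 4.
- Share ever controlled: E = 1 − (1−h)^4.
- Responders-only average: 30 × Σ k·p(k) / E.
- Restricted mean to day 120, all patients: 30 × Σ k·p(k) + 120 × (1−E).

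**Worked case, h = 0.1.** The p(k) are 0.1, 0.09, 0.081 and 0.0729, so E = 0.3439. Σ k·p(k) = 0.1 + 0.18 + 0.243 + 0.2916 = 0.8146. Responders-only average = 30 × 0.8146 / 0.3439 = 71 days. Restricted mean = 24.4 + 120 × 0.6561 = 103 days.

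| h | Ever controlled | Responders-only average (days) | Restricted mean to day 120, all patients (days) |
|---|---|---|---|
| 0.1 | 34% | 71 | 103 |
| 0.2 | 59% | 67 | 89 |
| 0.3 | 76% | 62 | 76 |
| 0.4 | 87% | 57 | 65 |

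Across this range the responders-only average moves by 14 days and the restricted mean by 38.

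**Set against sampling error.** Choose h so that 20% or 80% of patients are ever controlled (4 or 16 of 20). The responders-only average is then 72.9 days (standard error 16.7) or 60.6 days (standard error 7.8). A fourfold difference in response moves the average by about 12 days, less than its standard error at the low rate. The restricted mean is 110.6 against 72.5 days. The Kaplan-Meier median is not reached in the first case and is day 60 in the second.

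**Limiting case.** Suppose responders have the same timing whatever their number, with a quarter reaching control at each visit. The responders-only average is then (30+60+90+120)/4 = 75 days whether 20%, 50% or 80% respond. The restricted mean is 111, 97.5 or 84 days.

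**Relapse.** Table 1 ends at Visit 4, and its home-monitoring footnote covers Baseline to Visit 3 only. A patient first controlled at Visit 4 has no later scheduled assessment at which relapse could be seen. In the same model such patients are 0.0729/0.3439 = 21% of those ever controlled at h = 0.1, and 0.0864/0.8704 = 10% at h = 0.4.

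**The case against.** The best defence is that the article does not say non-achievers are dropped. It is silent, and denominators and censoring rules are often left to a fuller document. It also allows medians, and a median over all patients with non-achievers ranked last would be sound. The point about silence is fair. But the article is not silent on the summary itself: it names an average, and an average does not exist for patients without a value unless some rule supplies one. The objection therefore softens the criticism from a stated bad rule to a badly chosen summary.

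Second, the average does respond to the response rate in the constant-chance model, and a reader will also see the four-month control proportion, relapses and dropouts. This stands, and it limits the harm. The four-month proportion is still not the share ever controlled, so the average's denominator cannot be recovered from it.

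Third, the illustrative schedule is simpler than the trial's. Home monitoring starts 15 days after a dose change, so control can be detected between visits. That changes the exact days, not the structure of the problem. Dropouts who had already reached control do have a value; only those lost before control lack one.

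A reader might go further and infer that a single reading below threshold counts as control, so that measurement noise creates both early control and later relapse. With an unchanged true systolic pressure of 145 mmHg and a visit-to-visit standard deviation of 8 to 10, the chance that at least one of four independent readings falls below 140 is 71% to 77%. The documents do not support stating this as the plan's rule. The blood pressure definition refers to office readings in the plural and does not say how home readings are combined. Two of the three glycaemic criteria rest on patients asked to "wear a continuous glucose monitoring device for a minimum of seven days at home". The 145 and the standard deviations are assumed, the calculation ignores the diastolic limit, which would lower the chance, and a standard deviation of 5 already brings it to 50%.

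A reader might likewise infer that the relapse proportion includes patients first controlled at Visit 4. The article does not state that denominator either way.

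**Conclusion.** The point holds for the choice of summary. As worded, the average can be computed only among patients who reach control, is bounded by about 120 days, and is a weak guide to how many respond: 71 to 57 days while the share ever controlled goes from 34% to 87%, against 103 to 65 days for the restricted mean over everyone. These sizes rest on an assumed constant monthly chance, control detected only at 30-day visits, and no dropout. That patients without control have no value does not depend on those assumptions.

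The consequence is moderate. The outcome is descriptive, the study disclaims efficacy, and the four-month proportion is reported beside it. No passage says that days to control or relapse will set the design of the later trial, so that should not be asserted. The point does not extend to a claim that the definition of control is wrong. It is worth correcting because a better summary is available from the data already planned.

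**What to change.** In each disease group, replace the average with a Kaplan-Meier estimate of time to first control in all patients entering at baseline, censoring those not controlled at their last assessment. An interval-censored estimate is an alternative, since control is seen only at assessments. Report:

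- the number ever controlled, out of all who entered;
- the cumulative proportion controlled by each visit;
- the median if it is reached, or the restricted mean to day 120, with a 95% confidence interval.

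Report relapse with a denominator of controlled patients who have at least one later assessment, and give that number.

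Keep the stated definition of control. Control confirmed at the next assessment can be added as a sensitivity analysis only: making it the main rule would redefine the outcome, could compare home with office thresholds, and would leave control first seen at Visit 4 unconfirmed.

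No new data are needed; only the outcome and analysis wording changes. The cost is a less favourable figure that will be imprecise with 20 patients per group. Censoring also assumes that patients lost before control would have fared like those who stayed, so the number lost should be shown beside the estimate.

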#### 2.3.3. Study Procedures

The patient flow is shown in Figure 1, and the study procedures with time points are detailed in Table 1. 

To optimise a single drug dosage, the CURATE.AI system requires three data points (drug/dosage input and corresponding response) to calibrate to each individual patient before dosing recommendations can be given. At the point of recruitment, the treating physician will identify a principal medication (that will be modulated by CURATE.AI), and the patient medical records will be mined for previous data on the principal drug use and corresponding treatment response. If previous data are unavailable (none or only partially available), clinic visits will be scheduled until three such data points are obtained. Once three data points have been collected, the patient will enter the study at baseline and will be followed up for up to four clinic visits. Data will be collected and entered into the algorithm by a research assistant (Table 1). The intention is to generate dosing recommendations live (i.e., within a clinic visit). Workflows will be assessed during the qualitative interviews with staff. 

The frequency of data collection (i.e., monthly or for home monitoring, two weeks after dose change) was established by mutual agreement by the study team based on two main points. Firstly, the clinical team indicated that a monthly follow-up frequency was the maximum that would be acceptable to patients without being burdensome. Secondly, although the drugs used to control hypertension and type II diabetes can exert their effects in a matter of hours, medications take time to reach a steady state and produce their maximum effect. For example, the European Society of Cardiology recommends increasing the dose for angiotensin converting enzyme inhibitors (a common drug used in hypertension) every two weeks when titrating [27], while weekly dose increases have been suggested for metformin use in type II diabetics [28]. The viability of the proposed data collection frequency will form part of the feasibility evaluation.

Socio-demographics (age, sex, race, marital status), lifestyle factors (diet and physical activity), medical history and other clinical variables will be collected at baseline and select clinic visits (Table 1). Medication history and changes in medication dose (other than the principal medication) will be collected and monitored throughout the study. Dietary practices will be assessed using the Dietary Practice Questionnaire (26 items). The questionnaire was previously used in Singapore’s National Population Health Survey [29]. Physical activity will be assessed using the Global Physical Activity Questionnaire (GPAQ), originally developed by the World Health Organization (WHO). The GPAQ has been validated in Singapore [30,31] and includes three domains: activity at work, travelling to and from places, and recreational activities. Current medication adherence will be assessed using the 9 item Hill-bone medication adherence scale, validated for use in chronic disease patients [32]. Renal function will be measured using the estimated glomerular filtration rate and liver function by measuring aspartate aminotransferase and alanine aminotransferase. Any disagreement between the CURATE.AI recommended dosing decision and the physician’s opinion will be documented. In cases of dispute, we will collect information on the final dosing decision and the reasoning behind the decision. At any point when the physician disagrees with the CURATE.AI recommendation, the physician’s opinion will supersede the CURATE.AI dosing decision. If a physician overrides a CURATE.AI decision, the participant will remain on the study until completion regardless.

Participants will be followed up monthly for four months. Clinically, blood pressure may be controlled with medication within four to six weeks [33]. For type II diabetes, although traditionally changes in HbA1c are assessed every three months, emergent evidence suggests clinically relevant changes may occur as early as one month [34]. Based on these data, four months was deemed appropriate to observe clinical improvements as well as being a sufficient period to test the system. Clinic visits may be face-to-face or virtual as appropriate. If a dosage change is required at a clinic visit, hypertensive participants will be asked to monitor their ambulatory blood pressure for a single six-hour period at home (once hourly). A six-hour ambulatory blood pressure recording is equivalent to a twenty-four-hour reading [35]. Patients will then continue to monitor blood pressure twice daily, morning and evening, for up to seven days. Following any change of type II diabetic medications, patients will be asked to wear a continuous glucose monitoring device for a minimum of seven days at home (the maximum wear time is fourteen days). Monitoring will commence fifteen days after the dose change is initiated (for either hypertensives or type II diabetics), so a steady state can be reached before assessment. These data will feed back into the CURATE.AI system, and further recommendations on dose adjustment will be generated if required. The treating physician will regularly review remote monitoring data for safety. If the patient’s medication is changed entirely, recalibration with CURATE.AI is required. At the last clinic visit, patients will be interviewed using a semi-structured survey on their experiences with the CURATE.AI system. 

#### 2.3.4. Implementation Evaluation 

The implementation evaluation will be guided by modified versions of ‘The Non-adoption, Abandonment, Scale-up, Spread, and Sustainability’ (NASSS) framework and the Higgins & Madai (2020) framework on the development of artificial intelligence systems in healthcare [36,37]. The NASSS framework consists of six domains: the condition, the technology, the value proposition, the adopter system, the health or care organisation(s), and the wider context. The AI framework comprises of four domains: clinical validation, regulatory affairs, data strategy, and model development. Each domain identifies the risks, objectives, types of results and key advice from product development to market launch. These frameworks will assist in identifying factors that can influence the implementation of the proposed CURATE.AI system and its effectiveness. As this is a feasibility study, we will only focus on domains relevant to this stage of development (Table 2).

##### Patient Survey

All study participants will be invited to complete an experience survey based on an adapted version of the Singapore outpatient experience survey. This survey is routinely administered at specialist outpatient clinics and covers topics on the clarity of communication, professionalism, and service organisation [38]. We have modified this instrument to include open-ended questions on the experiences of CURATE.AI-guided dosing, appointment attendance, and ease of home monitoring (Supplement S1). If the participants cannot complete the survey or attend the last clinic appointment, they will be followed up with on the phone. A researcher will administer the interviews in English, Chinese, or Malay, according to patient preference. The survey will be piloted, for clarity, with volunteers not involved in the study before use.

##### Staff Interviews

Staff with experience of using the CURATE.AI system with at least one patient will be invited to participate in an in-depth interview. Participants will be approached in person or via email, emphasising that the interview is voluntary and that they may withdraw at any time. A purposive sample of participants will be recruited for maximum variance in professional roles and experience. Recruitment will occur on a rolling basis until data saturation has been reached. Interviews will be conducted using a semi-structured interview guide, including topics on the unmet needs of physicians when titrating medications in chronic disease patients, experiences of using the CURATE.AI system, perceived barriers and facilitators of using CURATE.AI in clinical practice, and how CURATE.AI could be integrated into existing workflows. Example questions include:Has CURATE.AI impacted your workload?What challenges have you faced when using CURATE.AI?What have been the expected and unexpected outcomes, both positive and negative, of using CURATE.AI?

The interviews will be conducted in a quiet, private meeting room, away from the clinic and ward areas, to encourage relaxed and open conversations. Interviews will be audio recorded and later transcribed for analysis.

#### 2.3.5. Data Analysis

All analyses will be conducted using STATA version 15.0 (STATA Corp, College Station, TX, USA). As appropriate, summary statistics will be presented as means with standard deviation, medians with interquartile ranges, and percentages. Clinical outcomes will be analysed separately for the hypertensive and type II diabetic groups. Blood pressure control is defined as a home or ambulatory blood pressure of less than 135/85 mmHg or office readings below 140/90 mmHg, unless otherwise defined by the treating physician [39]. Glycaemic control is defined as HbA1c < 7% [40] or glycaemic variability ≤ 36% or time in normal range (4.0 to 10.0 mmol/L) > 70% [41]. The proportion of patients achieving blood pressure control and glycemic control will be calculated by comparing the baseline reading to the four-month follow-up. A within-subject analysis of hypertensive and glycemic control will be conducted using the Chi^2^ or McNemar’s test, if cell counts are small (<5). The proportion achieving clinically relevant reductions in systolic and diastolic blood pressures by the four-month follow-up will be determined. The number of days until blood pressure or glycaemic control is first achieved will be calculated. The occurrence of relapse after control has been achieved (i.e., high blood pressure) will also be determined. 

Compliance with clinic follow-up will be calculated based on the number of scheduled sessions compared to attendance. Compliance with home monitoring will also be determined by remote receipt of data at scheduled time points. The proportion compliant with the home-monitoring schedule and the proportion of patients who drop out from the study will be reported. The number of disagreements between the CURATE.AI dosing recommendations and the physician’s opinion will be quantified. Success of the alignment on dosing decisions is defined as agreement with ≥70% of dosing decisions generated by CURATE.AI. The proportion of participants reaching this criterion will be derived. We will also summarise the reasons for disagreement and the magnitude of differences in dosing decisions, if it occurs. A sub-analysis will be conducted for participants whose dosing decisions were all based on CURATE.AI recommendations versus those who had one or more dosing decisions overridden by the treating physician. The purpose is to explore whether adherence to CURATE.AI confers an advantage in achieving clinical outcomes. Significance will be set at *p* < 0.05.

For interviews, audio recordings of the interview will be transcribed and translated into English (if necessary). A second independent researcher will check the accuracy of the translation. Data will be analysed using a thematic analysis method. Data will be coded according to the meaning of the sentences, followed by developing sub-themes and main themes. Qualitative data will also be organised according to the framework domains (Table 2).

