##### Exclusion Criteria

Patients with cognitive impairment.

Patients with active cancer undergoing chemotherapy.

Patients on haemodialysis or peritoneal dialysis (which can cause rapid fluctuation of BP and blood sugar, respectively).

Pregnant patients.

Patients with type II diabetes and hypertension whose medications are changed simultaneously during their first clinic visit.

Patients with controlled HbA1c or blood pressure at baseline.

Serious concomitant disorders that would compromise the safety of the patient or their ability to complete the study. This may include a recent occurrence of stroke or sub-arachnoid haemorrhage in hypertensive patients, which necessitates tighter control, and occurrence of renal failure or lactic acidosis in patients with type II diabetes, which may warrant avoidance or reduction in metformin dose.

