**CURATE.AI variables:**					
Retrospective dose-response data mined	X				
Hba1C ^a^ or blood glucose	X	X	X	X	X
Blood pressure	X	X	X	X	X

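### Low glycaemic variability alone counts as glycaemic control, so steady high glucose can score as a success, and entry was not judged on that measure

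*Protocol article*

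**What the plan says.** Section 2.3.5 (Data Analysis) of the protocol article gives the definition: "Glycaemic control is defined as HbA1c < 7% [40] or glycaemic variability ≤ 36% or time in normal range" of 4.0 to 10.0 mmol/L for more than 70% of the time. The three criteria are alternatives. No ranking is given, and nothing ties the variability criterion to a glucose level.

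The definition feeds two outcomes for the diabetic group. One is listed in section 2.3.2: "Proportion achieving blood pressure and glycaemic control at four months". The other is in section 2.3.5: "The number of days until blood pressure or glycaemic control is first achieved will be calculated". Section 2.3.5 also plans a within-subject comparison of the baseline reading with the four-month reading by a chi-squared or McNemar test, and significance is set at p < 0.05.

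Three further places matter:

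- **Entry.** The exclusion criteria list "Patients with controlled HbA1c or blood pressure at baseline". For glucose, HbA1c is the only measure named.
- **Source of the sensor measures.** Section 2.3.3 says: "Following any change of type II diabetic medications, patients will be asked to wear a continuous glucose monitoring device". Wear lasts at least seven days and starts fifteen days after the dose change.
- **Visit schedule.** Table 1 lists "Hba1C ^a^ or blood glucose" at baseline and at every visit. It schedules no sensor wear as a baseline assessment; its footnote only allows home monitoring after a dose change.

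**The concern.** HbA1c and time in range both describe the glucose level. Variability describes spread around whatever level the patient has. Because the criteria are alternatives, a patient who fails both level-based criteria is still controlled if the trace is steady enough.

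The second problem is asymmetry over time. A diabetic participant is admitted because HbA1c is not controlled. At follow-up the same person can be called controlled on HbA1c, on time in range or on variability. A participant whose glucose was already steady but high at entry, with nothing changed since, moves from uncontrolled to controlled once a sensor is worn. At stake are the proportion controlled at four months with its significance test, and the days to first control.

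**Working it through.** The plan states no figure on this point that could be reproduced. The check applies the rule as written to assumed glucose profiles.

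**Inputs from section 2.3.5.** Level criterion: "time in normal range (4.0 to 10.0 mmol/L) > 70"%. Variability criterion: "glycaemic variability ≤ 36"%. Any one criterion suffices.

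**Assumptions.** Variability is read as the coefficient of variation, CV = SD/mean. The document does not name the index; the percentage unit suggests this one. Means and CVs are illustrative. HbA1c is taken to be 7% or above in these profiles, since the document gives no conversion from mean glucose.

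**Step 1: time in range (TIR).** With SD = CV × mean, the normal form is TIR = Φ((10 − mean)/SD) − Φ((4 − mean)/SD). The lognormal form uses log-scale SD s = √ln(1 + CV²) and log-scale mean ln(mean) − s²/2.

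For mean 14 and CV 30%, SD = 4.2. Normal: Φ(−0.952) − Φ(−2.381) = 0.170 − 0.009 ≈ 0.16.

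For mean 12 and CV 36%, SD = 4.32. Normal: Φ(−0.463) − Φ(−1.852) = 0.322 − 0.032 = 0.29.

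| Mean (mmol/L) | CV | TIR, normal | TIR, lognormal | TIR > 70%? | CV ≤ 36%? | Scored as |
|---|---|---|---|---|---|---|
| 10 | 36% | 45% | 56% | no | yes | controlled |
| 12 | 36% | 29% | 36% | no | yes | controlled |
| 14 | 30% | 16% | 16% | no | yes | controlled |
| 16 | 20% | 3% | 1% | no | yes | controlled |

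Across the assumed grid of means 10 to 18 mmol/L and CVs 15% to 36%, TIR runs from 0% to 56%. Every profile fails the level criterion and every one is scored as controlled.

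**Step 2: direction of the index.** Hold SD at 4 mmol/L. At mean 10, CV = 4/10 = 40%, which fails; normal TIR is Φ(0) − Φ(−1.5) = 0.500 − 0.067 = 43%. At mean 16, CV = 4/16 = 25%, which passes; TIR is 6.5% (normal) or 3.7% (lognormal). With fixed spread, a rise in glucose turns a failure into a success.

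**Step 3: baseline against four months.** If every diabetic participant enters uncontrolled on HbA1c and that is the baseline status, no one can move from controlled to uncontrolled. For b conversions and no reversals, the exact two-sided McNemar p-value is 2 × 0.5^b. That is 0.063 for b = 5 and 0.031 for b = 6. Six conversions of any origin, including by variability alone, would therefore be significant at the stated level. This shows how sensitive the test is; it does not predict how many conversions would occur.

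**The case against.** **Whichever measure is available.** The alternatives could be read this way, as with home or office blood pressure in the same section. This does not rescue the rule. The two blood pressure criteria measure the same quantity. Variability and time in range come from one sensor trace, so both are available together and a passed variability criterion overrides a failed time in range.

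**The index is not named.** This stands as a caveat: the percentages above rest on reading it as SD/mean. The core point does not, because no measure of spread shows that the level is in target.

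**Feasibility only.** Section 2.3.2 says the main purpose is feasibility rather than efficacy, and the limitations section repeats this. The objection stands as to severity. Control is still the first listed clinical outcome and is tested, and the Discussion says the data will inform a later efficacy evaluation.

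A reader might also infer more than the document supports:

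- *A headcount.* If 30% to 80% of uncontrolled patients had low variability, 6 to 16 of 20 would be misclassified. That requires all 20 to have sensor data and to remain uncontrolled on both other criteria, and the document gives no basis for the share.
- *A missing endpoint.* Blood glucose in Table 1 might be taken as a single spot value that fits no criterion. The table does not say so, and the term could cover sensor data.
- *Relapse.* It is described only as high blood pressure, so the text does not show that a glycaemic relapse outcome is affected.
- *More dose changes, more chances at four months.* The proportion rests on the four-month reading. Repeated opportunities bear on days to first control.
- *Time in range is also invalid.* It measures level, and nothing here counts against it.

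**Conclusion.** The concern holds in a limited form. As written, variability of 36% or less is sufficient for glycaemic control, and patients far from the protocol's own time-in-range criterion can meet it: about 16% in range at mean 14 mmol/L with CV 30%, and 29 to 36% at mean 12 with CV 36%. These sizes rest on assumed profiles, normal or lognormal glucose, and the SD/mean reading. The asymmetry between entry on HbA1c and follow-up with added sensor routes is in the text. It can produce apparent improvement without any change in glucose, in the proportion controlled and in the days to first control. The number of participants affected cannot be estimated from the document. Severity is moderate: the control outcome should be corrected, but the feasibility conclusions do not depend on it.

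**What to change.** 1. In section 2.3.5, remove variability of 36% or less as a stand-alone route to control. Report it as a separate sensor outcome among those monitored, and name the index.
2. For the within-subject comparison, use one measure at both times: HbA1c against the protocol's own 7% threshold, obtained at baseline and Visit 4 for every diabetic participant.
3. Time in range above 70% may stay as a separately reported, level-based outcome among those monitored.
4. State which of the retained measures defines the days to first control.

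The cost is a wording change, plus HbA1c at two visits where Table 1 already lists it as an option. The reported control rate will be lower, and HbA1c lags late dose changes; the separate time-in-range result partly offsets that. The change removes the mismatch of measures only. Because participants are selected as uncontrolled at entry, the before-and-after test will still run in one direction and should be read descriptively.
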